### Secondary outcomes

A number of secondary outcomes such as number of children diagnosed with ASD, satisfaction with the navigator, and an array of parent-reported measures (e.g. parenting stress, social support, and coping responses) and are assessed (see Table 1 for full list of measures) at the time of entry into the study, as well as at three follow-up time points. Additional process outcomes will include confirmatory screening results, referrals to care, and service use and are obtained from care manager and navigator logs and from the child’s medical, early intervention, and ASD service provider records.

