### Control and intervention groups

#### Control

The control arm of this study receives Conventional Care Management consistent with the type of care provided within a traditional - but high quality – medical home. The care manager is available by phone to provide families with phone numbers and resources related to parents’ concerns about their child’s appointment, diagnosis, or developmental services.

The care manager contacts families by phone after randomization to introduce herself and remind families of their first appointment at the developmental clinic for their child’s ASD evaluation. The child’s primary care clinician also receives a letter from the care manager informing the clinician that the family has been assigned a care manager. The letter also contains the care manager’s contact information. After the care manager’s introductory phone call and letter, she remains available to the child’s family and other members of the care team if and when they initiate contact.

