### Intervention

PN is a theory-based, empirically-supported, multicomponent, manualized care management strategy [26, 27]. It differs from other care management strategies in that it focuses on overcoming patient-specific barriers to a defined set of services over a defined, time-limited period. PN is well established in cancer care as a means to reduce disparities in the critical interval between a positive screening test (for example, a mammogram for breast cancer) and definitive diagnosis [16, 17, 28], decrease anxiety [29], and increase satisfaction with services [29]. The goal of PN is to integrate a disjointed health care system on behalf of an individual patient. In our proposal, we build upon the established principles of PN but expand the navigator role in novel ways. Navigation services are provided to the family unit by bilingual paraprofessionals. It is extended to integrate a fragmented network of ASD services that requires coordination among community-based and educational services, as well as those provided by the conventional health care team.

Additionally, PN is augmented with evidence-based behavior change strategies – motivational interviewing and collaborative decision making – that support patient engagement and self-management skills. A typical PN activity may be to assist a parent with marginal literacy to complete a clinic’s patient questionnaires, help a family know what to expect during a stressful ASD diagnostic evaluation, or coordinate childcare around a child’s early intervention schedule. In this proposal, the systemic PN protocol begins after referral for an autism evaluation and end 100 days after diagnostic resolution – at which time, a child with ASD would be expected to be engaged and retained in intensive early intervention services (based on the guidance from Autism Speaks) [30]. Navigators follow a standardized protocol, keep extensive structured logs of their work, and a random subset of encounters are audio recorded. Data are captured on all interactions with families, providers, medical, educational, and social service organizations, recording time spent, activities performed, and barriers addressed.

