### Randomization process

We use stratified, blocked (randomly varying blocks of 2 and 4) randomization to allocate participants to Navigation or CCM. Randomization occurs independently at each primary care recruitment site. Randomization lists are generated in a secure web-based data management system. All outcome assessors are blinded to participant allocation. Written and verbal informed consent is obtained by research staff prior to randomization. Data will be collected in stored in StudyTrax, a commercial clinical research data management tool.

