### Effectiveness outcomes

#### Primary outcomes

The study’s primary outcomes are access to screening, diagnostic, and evidence-based service outcomes (Table 1). The trial measures diagnostic interval (number of days from positive screen to diagnostic determination) and time to receipt of ASD services/recommended services (number of days from date of diagnosis to receipt of services) from review of child’s medical and early intervention records in those with PN compared to CCM.

**Table 1 Tab1:** Diagnostic and Service Outcomes (primary outcomes)

Outcome	Measures	Response	Description
Expedited Evaluation	Achievement of Diagnostic Resolution	Yes/No	Percent children who complete diagnostic assessment within 12-month follow-up
	Timing of Diagnostic Resolution	Timely	Timely- Diagnostic interval ≤ 120 days
		Delayed	Delayed- Diagnostic interval > 120 but ≤ 180 days
		Unresolved	Unresolved - No resolution by 12-months
	Diagnostic Interval	Number of Days	Beginning the day of the positive confirmatory screen and ending the day when family receives determination (yes/no) of ASD diagnosis
Referral to Treatment	Time to receipt of EI services	Number of Days	Days from failed M-CHAT to receipt of services
	Time to receipt of ASD services	Number of Days	Days from Date of diagnosis to ASD services
Engagement in Treatment	Hours of services	Number of Hours	Hours ASD specialty services
	Adequacy of Services	Yes/No	Based on guideline of 25 h/ week
	Absenteeism	Number of absences	Number of family-initiated “no show” and cancellations divided by the number of scheduled appointments in 6 month period following diagnosis
Determination of ASD Diagnosis	ASD diagnosis	Yes/No	Based on ADOS evaluation by Board Certified DBP
Satisfaction with ASD-Services	Client Satisfaction Questionnaire [50]	Categorical and numerical	Previously validated measure of satisfaction with services
	Satisfaction with Hospital Care Questionnaire [50]	Categorical and numerical	Previously validated measure of satisfaction with services
Satisfaction with Navigator	Patient Satisfaction with Interpersonal Relationship with Navigator [51]	Categorical and numerical	Newly validated 9-item scale to assess satisfaction with the interpersonal relationship with navigators

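### Referrals and service use are ascertained partly from arm-specific logs that differ by design, which may tilt between-arm comparisons of these process outcomes towards PN

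*Protocol article*

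**What the plan says.** All references are to the Protocol article.

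- **Secondary outcomes.** The sources of three process outcomes are fixed in one sentence. It lists the results of confirmatory screening together with "referrals to care, and service use and are obtained from care manager and navigator logs", and in addition "from the child’s medical, early intervention, and ASD service provider records".
- **Intervention.** In the PN arm, "Navigators follow a standardized protocol, keep extensive structured logs of their work, and a random subset of encounters are audio recorded". The scope is wide: "Data are captured on all interactions with families, providers, medical, educational, and social service organizations".
- **Control.** The care manager makes an introductory call and sends a letter to the primary care clinician. After that she is available to the family and care team "if and when they initiate contact".
- **Primary outcomes.** Diagnostic interval and time to receipt of services are taken "from review of child’s medical and early intervention records in those with PN compared to CCM". Logs are not named there.
- **Randomization process.** "All outcome assessors are blinded to participant allocation".

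**The concern.** Each type of log exists in one arm only, and a log can hold only what its author learns. Proactive contact in PN against reactive contact in CCM is the intervention contrast itself, so the logs cannot be expected to detect events equally well. If an event counts when it appears in either source, the records treat the arms alike but the logs do not. Part of any difference in referrals or service use could then reflect who was watching rather than what the families received.

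Access to services is what the trial is about, so a service-use comparison open to this criticism would be easy to dismiss even if the effect were real. There is also a tension over blinding: anyone who derives an outcome from a navigator log or a care manager log can tell which arm the child is in.

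**Working it through.** The plan gives no figure for ascertainment, so there is none to reproduce. The check asks how large a spurious difference the stated sources could create.

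**Inputs from the article.** 125 participants per arm (Abstract, Methods); two-sided alpha 0.05 (Sample size and power); planning rates for service receipt of 60% and 80% (Time to receipt of recommended services), used here only as plausible event rates.

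**Assumed inputs, not in the article.** Record capture *r*, the same in both arms; log recovery *l*, the share of events missed by records that the arm's log picks up. An event counts if either source shows it.

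**Formulas.** With true rate *p* equal in both arms:

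- Observed rate = *p* × [*r* + (1 − *r*) × *l*]
- Spurious difference = *p* × (1 − *r*) × (*l* in PN − *l* in CCM)
- Rejection rate: two-proportion z test, pooled standard error for the critical value, unpooled standard error for the spread.

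**Worked case:** *p* = 0.60, *r* = 0.80, *l* = 0.50 (PN) and 0.10 (CCM).

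- PN: 0.60 × (0.80 + 0.20 × 0.50) = 0.540
- CCM: 0.60 × (0.80 + 0.20 × 0.10) = 0.492
- Difference: 0.048
- Pooled SE: √(2 × 0.516 × 0.484 / 125) = 0.0632; critical difference 1.96 × 0.0632 = 0.1239
- Unpooled SE: √[(0.540 × 0.460 + 0.492 × 0.508) / 125] = 0.0631
- Rejection: Φ[(0.048 − 0.1239)/0.0631] + Φ[(−0.048 − 0.1239)/0.0631] = 0.115 + 0.003 ≈ 0.118

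**Range over record completeness** (no true effect; difference in points, then rejection rate):

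| Record capture | p = 60%, logs 50% v 10% | p = 60%, logs 80% v 20% | p = 80%, logs 80% v 20% |
|---|---|---|---|
| 100% | 0; 0.05 | 0; 0.05 | 0; 0.05 |
| 95% | 1.2; 0.05 | 1.8; 0.06 | 2.4; 0.07 |
| 90% | 2.4; 0.07 | 3.6; 0.09 | 4.8; 0.14 |
| 80% | 4.8; 0.12 | 7.2; 0.21 | 9.6; 0.39 |
| 70% | 7.2; 0.21 | 10.8; 0.40 | 14.4; 0.69 |

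Halving the log recovery in the worked case (25% v 5%) halves the gap to 2.4 points, with rejection 0.07.

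**After the fix.** With records only, *l* = 0 in both arms. The difference is 0 and the rejection rate stays at 0.05 for every record capture from 70% to 100%.

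**The case against.** The other side has a good deal to say.

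- **There is a shared source.** The same sentence names medical, early intervention and ASD service provider records alongside the logs. If these are nearly complete, the bias is close to nil. This stands, and it is why the point is a risk and not a demonstrated bias.
- **These are process outcomes.** The article calls them additional process outcomes, and the main-effects analysis names no log-derived comparison. This stands and limits the weight of the point.
- **The primary outcomes might seem to be reached.** A reader might infer this because service use is close in content to Table 1, which is headed as primary outcomes and lists hours and adequacy of services. The text does not support that. The two primary time outcomes come from record review, and no source is stated for hours or adequacy. A condensed article may leave that detail to the full protocol, so its absence is not a fault.
- **The direction is not uniform.** Confirmatory screening largely precedes the intervention, so differential logging has little scope there. The concern is confined to referrals and service use.
- **The care manager's log is not described.** Its lower yield is inferred from the contact schedule. The inference is reasonable, but the recovery rates remain assumptions.
- **Blinding.** A reader might infer an outright contradiction. The article does not say that a blinded assessor reads the logs; other staff could extract or mask the data. It is a tension, not a proven conflict.

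What the objections do not remove is that the article itself names an arm-specific source for outcomes listed under effectiveness. The shared records do not cancel the effect unless they are complete or the two logs recover missed events equally, and the article supports neither.

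**Conclusion.** The point holds as a conditional one. The stated sources allow differential ascertainment of referrals and service use, and the likely direction favours PN. Under the central assumptions (true rate 60%, records capture 80%, logs recover 50% v 10% of misses) the gap is about 5 points and the false-positive rate about 12% instead of 5%. Across the assumptions tried in the table it runs from nil to about 14 points. Record completeness decides where in that range the trial lies, and the article does not give it.

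A reader might go further and say that PN is bound to show more events, or that a null comparison would be significant nearly half the time. With the central capture rates, a figure of that size (about 45%) needs a true event rate near 100%, well above the article's planning rates of 60% and 80% for service receipt, and it is not a fair headline. The point justifies a cheap improvement to the outcome definitions. It gives no reason to doubt the two primary time outcomes.

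**What to change.** - For between-arm comparisons of referrals and service use, count events only from the medical, early intervention and ASD service provider records, abstracted by the same procedure in both arms by staff who do not see the logs.
- Keep the logs for fidelity, dose and barriers. Report log-only events descriptively by arm, or add them in a sensitivity analysis labelled as such.
- Limit the blinding statement to outcomes derived from records.

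The cost is a change of wording and the loss of a few events known only from logs. The records are already being collected in both arms, so no new data source is needed.

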### Analyses

#### Intervention main effects

We will conduct an intention-to-treat (ITT) analysis where the denominator will include all children randomized to a treatment arm. For categorical outcomes we will use logistic regression models to compare the proportion of children who completed the diagnostic evaluation, and received recommended ASD specific services.

For time-to-event outcomes (time to diagnostic resolution, and time to receipt of ASD services) we will use censored analyses to construct Kaplan-Meier curves of time to event, and estimate hazard ratios, using Cox proportional hazard models.

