**Methods:**

This study uses a hybrid type I randomized effectiveness/implementation design to test effectiveness and collect data on implementation concurrently. It is a two-arm comparative effectiveness trial with a target of 125 participants per arm. Participants are families of children age 15–27 months who receive a positive screen for ASD at a primary care visit at urban clinics in Massachusetts (*n* = 6 clinics), Connecticut (*n* = 1), and Pennsylvania (*n* = 2). The trial measures diagnostic interval (number of days from positive screen to diagnostic determination) and time to receipt of evidence-based ASD services/recommended services (number of days from date of diagnosis to receipt of services) in those with PN compared to and activated control -Conventional Care Management – which is similar to care management received in a high quality medical home. At the same time, a mixed-method implementation evaluation is being carried out.

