#### Center effects

One of the strengths of our study is that each clinic site (center) is unique – in terms of its own clinical processes and the early intervention sites it has access to. By randomizing our sample separately within each center, we eliminate the potential of confounding by center. However, we will also examine potential clustering and assess effect modification by center [31], which will help us determine the generalizability of the PN model.

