### Sample size and power

According to Kraemer’s threshold of clinical significance concept [38], we estimate a required sample size of 250 to detect the smallest differences in primary outcomes that are of clinical importance. In the ITT analysis, we assess the adequacy of the expected sample to detect main effects among all children randomized, assuming a two-sided alpha of 0.05. We present power calculations for planned categorical analyses. Power to detect between group differences in analyses of count data will exceed those presented below.

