#### Time to receipt of recommended services

We assume that 80% in PN arm and 60% in the CCM arm will receive ASD services 5 months after a failed M-CHAT screen. A log rank test will have over 80% power to detect such differences as clinically significant at the 0.05 level.

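### Randomization is stratified by recruitment site, but the protocol article does not say that the primary Cox, log-rank and logistic analyses use those strata

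*Protocol article*

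**What the plan says.** All of this is in the protocol article.

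- **Randomization process:** "We use stratified, blocked (randomly varying blocks of 2 and 4) randomization to allocate participants to Navigation or CCM". The stratum is the clinic: "Randomization occurs independently at each primary care recruitment site". The abstract lists nine clinics (6 + 1 + 2) and a "two-arm comparative effectiveness trial with a target of 125 participants per arm".
- **Intervention main effects:** logistic regression for categorical outcomes. For time-to-event outcomes, Kaplan-Meier curves and a plan to "estimate hazard ratios, using Cox proportional hazard models". No site term or strata are named for either, and none are ruled out.
- **Time to receipt of recommended services:** "A log rank test will have over 80% power to detect such differences". Stratification is not mentioned.
- **Center effects**, under the mediator/moderator heading: "By randomizing our sample separately within each center, we eliminate the potential of confounding by center". The same section says each center has its own clinical processes and early intervention sites. It adds that clustering will be examined and effect modification by center assessed.
- **Moderation analyses:** site is one of two pre-named effect modifiers, with stratified analyses followed by interaction tests.

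**The concern.** Freedom from confounding is only one reason to carry the randomization strata into the analysis. Blocking within site forces the arms to balance on site, which removes the between-site part of the sampling variation in the treatment comparison. An unstratified standard error does not know this and still allows for that variation. If site predicts the outcome, the test then rejects less often than its nominal level.

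In Cox and logistic models, leaving out a prognostic factor also changes the quantity estimated. The result is a marginal ratio nearer 1 than the within-site ratio.

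The article itself gives reason to expect that site is prognostic. Clinical processes and service access bear directly on diagnostic interval and time to services, and the Setting section says the three states differ in their requirements for obtaining ASD services. At stake is part of the precision that stratified allocation was meant to secure. So is the timing of the decision: if the check for clustering is what decides how site enters the primary model, that choice is made after the data are seen.

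**Working it through.** **1. The plan's own power figures.** Inputs from the article: 125 per arm, two-sided alpha 0.05, services 80% v 60%, diagnostic completion 90% v 65%.

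- Services, under proportional hazards: HR = ln(1 − 0.8)/ln(1 − 0.6) = 1.609/0.916 = 1.756. Events = 125 × 0.8 + 125 × 0.6 = 175. Schoenfeld: z = √(175/4) × ln 1.756 − 1.96 = 3.73 − 1.96 = 1.77, so power is 96.1%. This meets the stated over 80%.
- Diagnostic completion: z = (0.25 − 1.96 × √(2 × 0.775 × 0.225/125)) / √((0.65 × 0.35 + 0.90 × 0.10)/125) = (0.25 − 0.1035)/0.0504 = 2.91, so power is 99.8%. This meets the stated > 90%.

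**2. Simulation set-up.** N = 250, nine clinics of about 28 children, blocks of 2 and 4 within clinic, exponential times, 60% control events at the end of follow-up and a common within-site HR of 1.76. The article gives no between-site spread, so the SD of the site log rate is assumed to be 0, 0.3, 0.5 or 0.8. For scale, clinics one SD above and one SD below the mean differ in rate by e^(2 × SD): 1.8-fold at 0.3, 2.7-fold at 0.5 and 5.0-fold at 0.8. Equal clinic sizes are also an assumption.

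**3. Estimates** (site effects fixed at normal quantiles, 1,000 trials per row).

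| SD | Mean HR, unstratified v stratified | Unstratified: model SE v actual spread | Stratified model SE |
|---|---|---|---|
| 0 | 1.77 v 1.77 | 0.154 v 0.156 | 0.156 |
| 0.3 | 1.73 v 1.77 | 0.154 v 0.147 | 0.157 |
| 0.5 | 1.65 v 1.76 | 0.155 v 0.147 | 0.159 |
| 0.8 | 1.55 v 1.77 | 0.156 v 0.131 | 0.162 |

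**4. Log-rank rejection rates, unstratified v stratified** (2,500 trials for power, 4,000 under no effect). The two figures on each side are for site effects fixed at normal quantiles and for site effects drawn at random in each trial.

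| SD | Power, % | Rejection under no effect, % |
|---|---|---|
| 0 | 96.2 / 95.8 v 95.8 / 95.3 | 4.5 / 5.1 v 4.9 / 5.0 |
| 0.3 | 94.2 / 95.1 v 95.0 / 95.6 | 4.8 / 4.5 v 5.2 / 5.0 |
| 0.5 | 92.3 / 92.4 v 95.1 / 95.0 | 3.1 / 4.0 v 4.7 / 5.5 |
| 0.8 | 85.1 / 86.2 v 94.4 / 94.0 | 2.0 / 2.7 v 5.1 / 5.3 |

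Monte Carlo error is about 0.4 points for a power near 95% and 0.3 points for a rejection rate near 5%. A smaller run with fixed site effects gave 84% v 94% power at SD 0.8, so the loss there is 8 to 10 points.

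**5. Check of the mechanism.** Under no effect at SD 0.8, the unstratified model SE is 0.164 against an actual spread of 0.136. The effective critical value is 1.96 × 0.164/0.136 = 2.36, a two-sided rate of 1.8%. At SD 0.5 it is 1.96 × 0.164/0.150 = 2.14, a rate of 3.2%. Both agree with the fixed-effect figures in step 4.

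**6. Logistic models** (2,000 trials). At 80% v 60% and SD 0.8, unadjusted v site-adjusted OR is 2.71 v 3.19 (within-site value 3.01), model SE 0.290 v 0.317 and power 96% v 97%. With 65% in both arms and SD 0.8, rejection is 4.3% v 5.9%. The consequence is small. Nine site terms also push the adjusted OR slightly past its target.

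**The case against.** The strongest reply is that the article is silent, not wrong. It names model families and never calls the main models unadjusted or unstratified. It is a condensed account, and strata and covariates are commonly left to an analysis plan that is not shown. A plain log-rank calculation is a routine planning device and does not fix the primary test. Site has clearly been considered, since it is a named effect modifier and clustering will be examined. The sentence on confounding is correct as written.

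Most of this stands. A reader might infer that the plan ignores site or has decided on unadjusted models, and the text does not support that. What remains is that the article does set out how center will be handled, in a section of its own, and confines it to confounding, a check and moderation. Site-specific results and interaction tests do not supply a site-stratified main effect, and the check for clustering has no stated consequence for the primary model.

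Three stronger technical readings also fail:

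- **Stratifying would shorten the intervals.** On the log scale it does not: the stratified Cox SE is slightly larger (0.157 to 0.162 v 0.154 to 0.156 for SDs of 0.3 to 0.8). The unstratified SE is too large only relative to that estimator's own spread. The gain comes from calibration and from the larger within-site estimate.
- **The unstratified ratio is biased.** The marginal HR or OR is a different estimand from the within-site one, not an erroneous one.
- **The power loss is decisive.** An assumed HR of 1.45 with 65% control events does give 62% v 69% at SD 0.5 and 47% v 65% at SD 0.8, but the article plans no such effect.

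**Conclusion.** The point holds as a worthwhile and nearly free improvement, chiefly for the time-to-event outcomes. It does not show that the trial is invalid or underpowered.

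If site is prognostic and omitted, the log-rank/Cox test rejects under no effect in about 3 to 4% of trials at SD 0.5 and about 2 to 3% at SD 0.8, and the HR of 1.76 reads as about 1.65 or 1.55. At the planned effect the power loss is negligible up to SD 0.3, 2 to 3 points at 0.5 and 8 to 10 points at 0.8. The error is conservative, so no false claim of benefit follows. Power stays above the promised 80% in every setting tried at the planned 80% v 60%. For the logistic models the loss is about one point even at SD 0.8.

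The size rests on the between-site SD, which the article does not give. It also assumes nine equal clinics, a common within-site effect and proportional hazards.

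**What to change.** State in Intervention main effects, or in the analysis plan, that the primary Cox models and log-rank tests are stratified by recruitment site and that the logistic models include site. Add a rule, set before unblinded data are seen, for pooling very small sites or sites with very few events within their network. Keep the planned site-interaction and moderation analyses as they are. Say also that the reported hazard and odds ratios are within-site effects.

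The cost is a sentence or two, since site is already recorded through randomization. If sites turn out not to differ, stratifying loses about one point of power (roughly 96% v 95%). In the logistic models, many site terms with sparse data can slightly overstate the OR, which is one reason for the pooling rule.
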